#### 2.4.2. Secondary Outcome

The secondary outcomes included widespread pressure pain sensitivity and temporal summation. All outcomes were assessed by using a digital pressure algometer (Force One FDIX, Wagner Instruments, Greenwich, CT, USA) with a round rubber surface of 1 cm^2^. Participants were supine. Algometry measurements were conducted at the following three locations bilaterally in the following order: common extensor tendon at the lateral epicondyle, tibialis anterior, and cervical spine. These locations were marked with a pen to assess all measurements at the same points.

Widespread pressure pain sensitivity was assessed by determining PPTs bilaterally in the treatment point (elbow), segmental-related point (cervical spine), and a distant non-related point (tibialis anterior). The pressure was applied perpendicular over each point at a rate of 1 kg/s approximately until the subject felt the first sensation of pain [32,33]. At this moment, the algometer was removed and the measurement value was recorded. Participants had two practice trials on the hand before the evaluation begins. Three measurements were obtained at each assessed point with a 30-s interval for avoiding temporal summation [34] and the mean was used for the analysis. If there was a difference of more than 1 kg/cm^2^ between two consecutive measurements at the same point, the highest value was removed and another measurement was obtained.

The evaluation of temporal summation (TS) began one minute after the end of the CPM assessment. The sequential stimulation of mechanical pressure stimuli consisted of 10 pressures with the algometer at PPT level (with 1-s interval between them) on each of the three assessed points, i.e., elbow, neck, and tibialis anterior [35]. The subjects were asked for rating their pain of the 1st and 10th pulse on a numerical pain rating scale (NPRS; 0 = no pain, 10 = maximum tolerable pain). The final rating of TS resulted from the difference between the 10th and the 1st pain rating scores [36]. Figure 1 graphs the experimental protocol timeline.

### 2.5. Sample Size 

The sample size was calculated for the primary outcome. Overall, an increase of at least 10% in PPTs following the conditioning stimulus was considered as an activation of CPM [31]. The determinations were based on detecting pre-post differences of 20% on PPTs following the conditioning stimulus with an alpha level of 0.05, and a desired power of 80%. This generated a sample size of at least 16 participants per group. Similarly, we calculated sample size according to clinically relevant changes. We estimated a large effect size of 1.05 (Cohen’s d) for changes in PPTs following the conditioning stimulus with a statistical power of 80% and an alpha error of 0.05. Therefore, we estimated 16 subjects per group, and considering a 10% lost, 18 individuals per group were recruited (72 subjects in total). GPower 3.1 program was used to calculate the sample size [37].

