Thus, the exact therapeutic mechanisms of percutaneous electrolysis are not completely defined, and both mechanical and biochemical effects are currently suggested [9]. Recently, it has been hypothesized that dry needling may produce neurophysiological effects integrated into a pain neuroscience paradigm, such as activation of central inhibitory pain pathways, analgesia, conditioned pain modulation, segmental inhibition, or release of endogenous opioids and other neurotransmitters [18,19,20]. These mechanisms should be included in the concept of endogenous pain modulation (EPM), which is the ability of the central nervous system to modulate the nociceptive input from peripheral tissues ascending from the spinal cord to the brainstem [21].

Endogenous pain modulation shows a clinical relevance and plays an important role in the experience of pain. In fact, although the intensity of a nociceptive input is significant for pain, the subsequent modulation of peripheral impulses conditions the intensity of the final painful sensation [22]. In this way, dysfunction of pain inhibitory ability has been associated with chronic pain states such as fibromyalgia, osteoarthritis, or temporomandibular disorders [23]. Further, it has been proposed that EPM efficacy may predict the analgesic effect in response to treatment and that even some therapies are able to potentiate the EPM [24]. No study has investigated the effects of percutaneous electrolysis in EPM. 

The primary aim of this randomized clinical trial is to investigate if the application of percutaneous electrolysis enhances EPM when compared with a simple needle application or no intervention in an asymptomatic healthy population. The secondary aim is to determine if the effects on EPM are different between the application of two different protocols (i.e., low intensity or high intensity of the electrical current) of percutaneous electrolysis. Thus, we first hypothesize that a single session of percutaneous electrolysis will be able to activate EPM in a greater manner than the application of dry needling. Our second hypothesis is that activation of EPM will be higher with the high-intensity protocol than with the low-intensity protocol.

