#### 2.4.1. Primary Outcome

The primary outcome was conditioned pain modulation (CPM), which was tested using the upper extremity submaximal effort tourniquet test [31]. Specifically, participants were asked to elevate their non-dominant upper extremity for one minute. A blood-pressure cuff was inflated to a pressure of 280 mm Hg. Participants rated the tourniquet-induced pain intensity of the upper extremity on an 11-point numerical pain rate scale (NPRS, 0–10). The cuff was deflated 6 min after, and 3 trials of pressure pain thresholds (PPTs) at the extensor tendon of the lateral epicondyle, cervical spine, and tibialis anterior muscle were obtained immediately following cuff deflation. Activation of CPM was operationally defined as an increase in PPTs of at least 10% following the conditioning stimulus (tourniquet test). These methods correspond to recommendations on practice of CPM testing [31].

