### 3.2. Limitations

It should be recognized that this protocol has some limitations. First, this study will include healthy participants, which will make it difficult to extrapolate the results to daily clinical practice. Nevertheless, we consider that it is highly important to determine the physiological effects of an intervention such as percutaneous electrolysis first in healthy individuals showing proper CPM and as a second step to determine its effects in different chronic pain conditions, where CPM is usually impaired and, therefore, the response maybe different. Second, another consideration is the inclusion of a non-intervention group to determine the effects of time on CPM. Additionally, although the participants will be blinded from their group assignment, some subjects may perceive discomfort related to the application of galvanic current and identify the intervention that they receive. Successfully blinding will be confirmed by asking the participants which intervention they believed had received. It should be recognized that it will be not possible to blind the therapist who will apply the interventions, considering the treatment approach that is proposed. It would increase the risk of bias due to deviation from intended interventions. Finally, the results of this study will be restricted to the immediate effects of assessments. Since this is a mechanisms-related study, this is the common procedure in published studies [40,41,42].

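### The stated 80% power is worded for the response to the tourniquet; for the between-arm aim it holds at most for one unadjusted pairwise contrast at a very large effect

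*Protocol article*

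**What the plan says.** All references are to the protocol article.

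- **Aim (section 1).** The trial is to "investigate if the application of percutaneous electrolysis enhances EPM when compared with a simple needle application or no intervention". This is a comparison between arms.
- **Primary outcome (2.4.1).** CPM is tested with a tourniquet as conditioning stimulus. "Activation of CPM was operationally defined as an increase in PPTs of at least 10% following the conditioning stimulus".
- **Timing (2.4).** All outcomes are measured before and after the intervention, in the order PPTs, CPM, temporal summation. Each participant therefore has an unconditioned and a conditioned PPT at both times.
- **Sample size (2.5).** "The sample size was calculated for the primary outcome". The first calculation: "The determinations were based on detecting pre-post differences of 20% on PPTs following the conditioning stimulus", with alpha 0.05 and 80% power, giving at least 16 per group. The second: "We estimated a large effect size of 1.05" (Cohen's d), again for PPT changes after the conditioning stimulus, and again 16 per group. Allowing for 10% loss gives 18 per group and 72 in total.
- **Analysis (2.8).** Repeated-measures ANOVA with Bonferroni post hoc tests, and mixed models with a group-by-time interaction.
- **Limitations (3.2).** The intervention is to be studied "first in healthy individuals showing proper CPM".

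**The concern.** Three quantities need to be kept apart:

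1. the CPM response: the PPT rise from before to after the tourniquet, at one assessment;
2. the change in that response from before to after the intervention, in one person;
3. the difference between arms in that change.

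The aim is about the third. Section 2.5 words both of its inputs as the first. It does so directly after repeating the 10% rule, which uses the same reference to the conditioning stimulus. Section 3.2 expects healthy participants to show this response without treatment, so it should appear in every arm, controls included, and does not separate electrolysis from needling.

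Section 2.5 gives no between-arm difference in CPM change, no SD and no comparator. A reader cannot tell what effect of electrolysis the trial is sized to find. The risk is that a null between-arm result is read as evidence of no effect in a trial with 80% power, when power for the actual question may be much lower.

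**Working it through.** **Inputs from the article.** d = 1.05; a 20% difference; alpha 0.05; power 80%; 16 per group, 18 after loss; four arms; Bonferroni post hoc tests.

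**Assumptions added here.** Two-sided t-tests, normal outcome, equal arms, all 4 × 3 / 2 = 6 pairwise contrasts. Power is from the noncentral t distribution. For two groups of n, the noncentrality is d × √(n/2) with 2n − 2 degrees of freedom.

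**Step 1. Reproduce 16 per group from d = 1.05.**

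| Test | n for 80% power |
|---|---|
| Two independent groups, two-sided | 15.26, so 16 per group (power at 16: 82.0%) |
| Two independent groups, one-sided | 12 per group |
| Paired, two-sided | 10 (n = 9 gives 78.7%, n = 10 gives 83.9%) |
| Paired, one-sided | 8 |

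Only the first row gives 16. The loss allowance also reproduces: 16 / 0.9 = 17.8, so 18, and 18 × 4 = 72.

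**Step 2. The 20% calculation.** It cannot be reproduced because no SD is given. For n = 16 it needs an SD of about 19.5 points as a two-group test, or an SD of change of about 26.7 points as a paired test.

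**Step 3. Reading A: d = 1.05 is a between-arm difference in CPM change.**

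| Alpha | Power at 16 | Power at 18 |
|---|---|---|
| 0.05, one contrast | 82.0% | 86.4% |
| 0.05 / 6 = 0.0083 | 56.3% | 63.7% |

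With six contrasts, 80% power at d = 1.05 needs 24 per group.

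**Step 4. Reading B: 20% and d = 1.05 describe the tourniquet response.** If both figures describe the same quantity, the SD of the CPM response is 20 / 1.05 = 19.05 points. Let r be the correlation between the response before and after the intervention, and suppose electrolysis adds 10 points. The 10 points and the range of r are illustrative; the article gives neither.

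- Change score, no baseline adjustment: SD = 19.05 × √(2(1 − r)), d = 10 / SD.
- Baseline-adjusted: residual SD = 19.05 × √(1 − r²), d = 10 / SD, with one degree of freedom fewer.

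| r | SD of change | d | Power at 16 | Residual SD | d | Adjusted power at 16 |
|---|---|---|---|---|---|---|
| 0.3 | 22.5 | 0.44 | 23% | 18.2 | 0.55 | 33% |
| 0.5 | 19.0 | 0.52 | 30% | 16.5 | 0.61 | 38% |
| 0.7 | 14.7 | 0.68 | 46% | 13.6 | 0.74 | 52% |

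These are for a single contrast with no multiplicity correction.

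**Step 5. Between-arm d detectable with 80% power.** One unadjusted contrast: 1.02 at 16 per group, 0.96 at 18. Bonferroni over six: 1.31 at 16, 1.22 at 18.

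**The case against.** The strongest defence is that the arithmetic is between-group. Sixteen follows from d = 1.05 only as an independent two-group test, and the wording could be loose shorthand for a change from before to after the intervention. The first calculation is compatible with this: as a two-group test it needs an SD of about 19.5 points, close to 20 / 1.05 = 19.0. Section 2.8 also plans a group-by-time interaction, which does test change between arms. All of this stands.

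It rules out three stronger readings that a reader might infer:

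- *That the 80% power has no bearing on the primary aim.* This is not supported. If 1.05 is a between-arm difference in CPM change, one unadjusted contrast has 82.0% power.
- *That the two calculations contradict each other.* This cannot be shown, because the SD behind the 20% is not given.
- *That the 10% rule sits at its ceiling at baseline and so cannot show enhancement.* With mean 20 and SD 19.05 under normality, about 70% of participants would meet it at baseline and about 85% after a 10-point gain. The rule is insensitive, but not saturated. Section 2.8 plans no test of it, so calling it descriptive is a minor clarification.

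The defence does not supply what section 2.5 omits: a statement that 1.05 is a between-arm difference, a reason to expect one that large, or an allowance for the Bonferroni tests.

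**Conclusion.** The point holds as a fault in how the power is stated and in what it covers. Section 2.5 claims 80% power for the primary outcome with inputs worded as the tourniquet response, and gives no between-arm difference in CPM change.

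On the reading most favourable to the plan, 80% holds for one unadjusted pairwise contrast at d = 1.05, and falls to about 56% (16 per group) or 64% (18) under Bonferroni over six contrasts. On the literal reading, power at 16 per group for a 10-point gain is about 23–46% unadjusted or 33–52% baseline-adjusted.

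The first pair of figures assumes that all six contrasts are tested. The second set also rests on an assumed SD of about 19 points, correlations of 0.3–0.7 and an illustrative gain, so it shows the order of size and is not an estimate for this trial. On neither reading is 80% established for the four-arm question.

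**What to change.** Keep n = 72 and make three changes:

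1. **Endpoint and analysis (2.4.1, 2.8).** Analyse CPM as continuous: conditioned minus unconditioned PPT after the intervention, compared between arms with adjustment for the same quantity before it. These measurements are already collected.
2. **Sample size (2.5).** Restate it as the between-arm difference in CPM that 16 to 18 per group can detect with 80% power: about d = 1.02 at 16 or 0.96 at 18 for one unadjusted contrast, and about 1.31 at 16 with Bonferroni over six. Give the assumed SD, the pre-post correlation and the number of contrasts. If d = 1.05 was meant as a between-arm difference, say so and justify it.
3. **10% rule (2.4.1).** State that the activation rate is descriptive.

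The cost is a change of wording and a baseline covariate, with no extra participants or measurements. The downside is that the stated power, or the detectable effect, will look less favourable than the present text suggests.

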### 2.8. Statistical Methods 

Data were analyzed by using the IBM-SPSS software package (version 26.0). The significance threshold was established at 0.05 and the limits of the confidence interval at 95%. Changes in outcomes were tested on the basis of the intention-to-treat principle. Firstly, the distribution of normality for all the variables was checked by the Shapiro–Wilk test. Then, a descriptive analysis of baseline characteristics of the sample was reported, calculating the means and standard deviations for those variables with normal distribution and the median and interquartile range for those with non-normal distribution.

Subsequently, to assess the effects of the interventions, we conducted repeated measures analysis of variance (ANOVA) tests for quantitative variables (or Kruskal–Wallis test for non-normal variables) and the Bonferroni test as post hoc comparisons. Mixed-effect regression models considering the group effect, time effect, and group x time interaction were conducted. 

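### The 80% power at 16 per group matches one unadjusted two-group comparison; under the planned Bonferroni comparisons of four groups, power per pair at d = 1.05 is about 60–67%

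*Protocol article*

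**What the plan says.** Section 2.5 (Sample Size) gives two calculations with the same answer. The first rests on "detecting pre-post differences of 20% on PPTs following the conditioning stimulus", with no standard deviation. The second uses a standardised effect, a Cohen's d of 1.05 that the section calls large, and is described as being "for changes in PPTs following the conditioning stimulus with a statistical power of 80% and an alpha error of 0.05". Both lead to 16 per group, raised to 18 for 10% loss, 72 in total. The section names no test, sidedness, comparator or adjustment for multiple comparisons.

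Section 2.6 randomises to four groups: control, needling, low-intensity electrolysis and high-intensity electrolysis. Section 2.8 (Statistical Methods) plans repeated measures ANOVA and mixed models with a group by time interaction, and names "the Bonferroni test as post hoc comparisons" without saying how many comparisons this covers.

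The Introduction states the primary aim as whether percutaneous electrolysis "enhances EPM when compared with a simple needle application or no intervention". The secondary aim is to compare the low- and high-intensity protocols.

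**The concern.** The sample size calculation and the analysis use different significance levels for the same question. Section 2.5 spends the full 0.05 on one comparison. Section 2.8 divides it across several, and section 2.5 makes no allowance for that. An overall test across four groups does not say which groups differ, so the stated aims are judged on the adjusted pairs.

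If those pairs have about 60% power, a true difference of the planned size would be missed about 4 times in 10, where the reader of section 2.5 expects 2 in 10. This matters most for electrolysis against needling. Section 3.1 attributes the analgesia to the galvanic current, and that comparison isolates the current. The planned d of 1.05 is already called large, so there is little room to assume a larger one.

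**Working it through.** **Inputs.** d = 1.05, alpha 0.05, power 80%, 16 per group evaluable and 18 recruited (section 2.5); four equal groups (section 2.6); Bonferroni post hoc comparisons (section 2.8). Assumptions: two-sided tests; d applies to the change that is analysed, as section 2.5 words it; six comparisons (all pairs of four groups, 4 × 3 / 2 = 6), varied below.

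**Formula.** For two groups of n, the t statistic has noncentrality d × √(n/2). Power is the probability that a noncentral t exceeds the two-sided critical value.

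**Step 1: reproduce the plan's figure.** With n = 16, noncentrality is 1.05 × √8 = 2.97. At alpha 0.05 with 30 df the critical value is 2.042 and power is 82.0%. With n = 15 it is 79.3%, so 16 is the smallest n that reaches 80%. Allowing for loss, 16 / 0.9 = 17.8, rounded up to 18. Other readings do not give 16: a one-sided two-group test needs 12, a two-sided paired pre-post test needs 10, and a one-sided paired test needs 8. So, although the text speaks of pre-post differences, the figures fit a comparison of two groups at full alpha.

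**Step 2: apply the planned adjustment.** For six pairs, alpha per pair is 0.05 / 6 = 0.0083. The pooled error of the four-group ANOVA has 4n − 4 df.

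- n = 16: df 60, critical value 2.729, noncentrality 2.97, power 59.7%.
- n = 18 (no loss): df 68, critical value 2.718, noncentrality 1.05 × √9 = 3.15, power 66.7%.

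Using only the two groups' own df (30 and 34), power is 56.3% and 63.7%.

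**Step 3: vary the number of comparisons** (single-arm pairs, d = 1.05, pooled df).

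| Pairs | Alpha per pair | Power, n = 16 | Power, n = 18 |
|---|---|---|---|
| 3 | 0.0167 | 69.3% | 75.5% |
| 4 | 0.0125 | 65.4% | 71.9% |
| 5 | 0.0100 | 62.2% | 69.1% |
| 6 | 0.0083 | 59.7% | 66.7% |

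Five is the count if each electrolysis arm is compared with needling and with control, plus low against high. With only two comparisons, 18 per group would just reach 80% (80.2%) and 16 would not (74.7%), but the aims name more than two.

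**Step 4: what the design can detect.** For six pairs with pooled df, power reaches 80% at d = 1.27 (n = 16) or d = 1.19 (n = 18). To have 80% power at d = 1.05 would take 23 evaluable per group, or 26 after 10% loss (23 / 0.9 = 25.6).

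**Step 5: the omnibus test.** For the four-group F test on changes at n = 16, with a largest difference of 1.05 SD:

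| Group means (SD units) | Power |
|---|---|
| 0, 0.525, 0.525, 1.05 | 67% |
| 0, 0.35, 0.70, 1.05 | 72% |
| 0, 0, 0, 1.05 | 85% |
| 0, 0, 1.05, 1.05 | 94% |

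**The case against.** Several points on the other side are sound.

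- **Six pairs and the sizing test are inferred.** Section 2.8 gives no number of comparisons and section 2.5 names no test. This stands. Six is the natural reading of Bonferroni comparisons after a four-group ANOVA, and the two-group t test is the only one of the readings tried that gives 16, but both are assumptions. Step 3 shows that the conclusion survives three to six pairs.
- **Bonferroni is post hoc to the ANOVA and the mixed model.** A reader might infer that the trial as a whole lacks power, or that 80% is reached for nothing but one unadjusted pair. The documents do not support that: the omnibus test exceeds 80% under some patterns of means. It does not, however, answer the aims as stated.
- **The repeated measures model may add precision.** It might, but section 2.5 attaches d to changes in PPTs and claims no further gain, and how d was standardised is not stated.
- **No false-positive risk arises.** Correct. Bonferroni controls the type I error, and comparing each electrolysis arm with needling is a legitimate way to address the primary aim. A reader might also infer that the authors will take a non-significant pair as proof of no effect. Nothing in the article says so.

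It is tempting to go further and replace the pairs with a fixed sequence led by both electrolysis arms pooled against needling (32 v 16, alpha 0.05). That is a trade-off and does not follow from this point. Its 92% power at n = 16 assumes d = 1.05 in both arms, whereas the second hypothesis expects high intensity to do better. Power falls to 72% if low intensity has half the effect and to 39% if it has none. In that last case, with high against low tested third in the sequence, power for that comparison would be about 17–22%, against 60–67% under the Bonferroni pairs.

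**Conclusion.** The point holds for the pairwise comparisons. Section 2.5's 80% is consistent with one unadjusted two-group comparison and is not delivered for the adjusted pairs that section 2.8 plans and the aims need. At d = 1.05, power per pair is about 60% (16 per group) to 67% (18 per group) for six pairs, and about 62–69% or 69–75% for three to five. This rests on two-sided testing, pooled ANOVA error and d applying to the change analysed. The objection to leaving this to the analysis plan does not apply, because both the unadjusted alpha and the Bonferroni comparisons are stated in this article. The defect is a misstated power figure; it neither invalidates the analysis nor shows that the trial as a whole is underpowered.

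**What to change.** Amend section 2.5 to state:

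1. that the 80% refers to one unadjusted two-sided two-group comparison at d = 1.05, if the authors confirm that this was the test used;
2. the number of comparisons that the Bonferroni correction in section 2.8 covers;
3. if that number is six, that power per adjusted pair at d = 1.05 is about 60% with 16 per group and 67% with 18;
4. that the effect detectable with 80% power per adjusted pair is then d of about 1.27 (16 per group) or 1.19 (18 per group).

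If fewer comparisons are meant, items 3 and 4 should be recomputed for that number. The change is to the wording of one section. It needs no more participants and leaves the planned analysis as it is. The downside is a less favourable stated power.
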